## Abstract

**Background:**

Aboriginal Australians are known to suffer high levels of acquired brain injury (stroke and traumatic brain injury) yet experience significant barriers in accessing rehabilitation services. The aim of the Healing Right Way trial is to evaluate a culturally secure intervention for Aboriginal people with newly acquired brain injury to improve their rehabilitation experience and quality of life. Following publication of the trial protocol, this paper outlines the statistical analysis plan prior to locking the database.

**Methods:**

The trial involves a stepped wedge design with four steps over 3 years. Participants were 108 adult Aboriginal Australians admitted to one of eight hospitals (four rural, four urban) in Western Australia within 6 weeks of onset of a new stroke or traumatic brain injury who consented to follow-up for 26 weeks. All hospital sites started in a control phase, with the intervention assigned to pairs of sites (one metropolitan, one rural) every 26 weeks until all sites received the intervention. The two-component intervention involves training in culturally safe care for hospital sites and enhanced support provided to participants by Aboriginal Brain Injury Coordinators during their hospital stay and after discharge. The primary outcome is quality of life as measured by the Euro QOL–5D-3L VAS. A mixed effects linear regression model will be used to assess the between-group difference at 26 weeks post-injury. The model will control for injury type and severity, age at recruitment and time since commencement of the trial, as fixed effects. Recruitment site and participant will be included as random effects. Secondary outcomes include measurements of function, independence, anxiety and depression, carer strain, allied health occasions of service received and hospital compliance with minimum processes of care based on clinical guidelines and best practice models of care.

**Discussion:**

The trial will provide the first data surrounding the effectiveness of an intervention package for Aboriginal people with brain injury and inform future planning of rehabilitation services for this population. The statistical analysis plan outlines the analyses to be undertaken.

**Trial registration:**

Australia New Zealand Clinical Trials Registry ACTRN12618000139279. Registered 30 January, 2018.

## Background

Brain injury resulting from both stroke and traumatic injury can have significant ongoing effects on survivors in terms of affecting their sense of self, social relationships, mental health and community participation including employment prospects [1, 2]. Family members’/carers’ quality of life can also be affected as their lives change when supporting the person with the brain injury [3]. For Aboriginal Australians, as for other Indigenous populations, stroke occurs at a higher rate than for their non-Indigenous counterparts, and at a relatively younger age, reflecting the high prevalence of comorbidities such as diabetes and chronic cardiovascular conditions [4–9]. Traumatic brain injury (TBI) is also known to occur at a higher rate [10, 11]. Previous research has highlighted mismatches between community needs and services currently offered to Aboriginal people with brain injury and their families/community [12–14]. This has resulted in limited ongoing engagement between Aboriginal people with brain injury and hospital-based rehabilitation services, with particular challenges for (although not limited to) those living in rural and remote areas. Aboriginal people with brain injury have highlighted the need for (i) services that respect and incorporate cultural protocols and values, (ii) culturally secure assessment and treatment tools, (iii) support after hospital discharge and (iv) Aboriginal health worker involvement in this support.

Healing Right Way is a stepped wedge trial that implements and assesses the impact of a research-informed culturally secure [15] intervention model for Aboriginal people with brain injury in eight hospital sites in Western Australia (WA). The trial is registered in the Australia New Zealand Clinical Trials Registry (ACTRN12618000139279) and has received multiple relevant ethics approvals. The main trial protocol [16] was published previously. The current version of the trial protocol is Version 5 dated 3/11/20. This document updates and extends the statistical analyses outlined in the protocol and describes the presentation of results for the principal paper(s) which will report the results of the primary and secondary effectiveness hypotheses.

## Study overview

### Aims and hypotheses

The primary hypothesis is:H1. Compared to usual care (UC), implementation of the proposed intervention package (IP) will result in a higher score on the Euro QOL–5D-3L [17] VAS at 26 weeks post-injury.

The secondary hypotheses are:H2. Compared to UC, implementation of the IP will result in an improvement in service delivery at 12 and 26 weeks post-injury as evidenced by increased occasions of service.H3. Compared to UC, implementation of the IP will result in an improvement in service delivery at 12 and 26 weeks post-injury as related to increased compliance with minimum process of care indicators.H4. Compared to UC, implementation of the IP will result in significant reduction in disability (Modified Rankin Scale, mRS) [18] and greater independence (Functional Independence Measure, FIM™) [19] at 12 and 26 weeks post-injury.H5. Compared to UC, implementation of the IP will result in significantly less carer burden (Modified Caregiver Strain Index) [20] and less brain injury survivor anxiety and depression (Hospital Anxiety and Depression Scale) [21] at 12 and 26 weeks post-injury.H6. The culturally sensitive IP will be more cost-effective (additional benefits gained will justify additional costs for delivering the intervention; may lead to potential cost-offsets from less severe disease) than UC 26 weeks post-injury.H7. The IP will be acceptable to health professionals and Aboriginal participants and their families, and the role of the Aboriginal Brain Injury Coordinator is a feasible one.

The primary hypothesis (H1) and the first four of these (H2–H5) will be the focus of this statistical analysis plan. Cost effectiveness (H6) will be assessed by the health economics expertise within the trial team and will be published separately. Acceptability and feasibility of the Aboriginal Brain Injury Coordinator intervention (H7) will be assessed using qualitative analysis methods as per the published protocol for the project’s Process Evaluation [22].

### Study design

Healing Right Way was planned as a stepped wedge trial with four steps over 3 years. Eight sites (four rural hospitals and four urban sites) are participating in the trial. The 3-year timeframe was divided into six 26-week periods. At the start of the trial, all sites were in the control condition which contributed a baseline measurement for all sites. The trial plan called for two sites cross over to the intervention condition, at the end of the first 26-week period, while the other sites remained in the control condition. At the end of the second 26-week period, two additional sites were to cross over from the control condition to the intervention condition, and at the end of the third 26-week period, the last two sites were to cross over to the intervention condition. Starting with the fifth 26-week period, all sites were to be in the intervention condition. The trial design allowed for one additional 26-week period in which all sites were to be in the intervention condition. We recruited fewer people than anticipated—especially in the initial periods after the trial commenced. The trial design was therefore modified to accommodate the reduced recruitment numbers. On advice of the Trial Management Committee, the trial design maintained four steps as planned, but the baseline extended period by an additional 26 weeks. The modified design is presented in Fig. 1.

**Fig. 1 Fig1:**
[figure not shown]
Implemented stepped wedge design

Participants were initially recruited within 4 weeks post-injury. This was amended during Period 1 to 6 weeks post-injury to enable recruitment of otherwise eligible patients who were only referred to the study immediately prior to the 4-week cut-off and for whom the recruitment process could not be organised within the short time frame. Outcome data were collected from participants and caregivers at 12 weeks and 26 weeks post-injury (as outlined in Table 1 below). Baseline assessments were predominantly conducted at the trial site at the time of recruitment. However, an amendment during Period 1 enabled recruitment in the community, to enable participants who were only referred to the study immediately prior to hospital discharge to be recruited. Participants were generally expected to have been discharged from the hospital sites prior to the 12-week and 26-week assessments. These assessments were therefore predominantly conducted off-site.

**Table 1 Tab1:** Schedule for collection of participant-level outcome measures

Data collection point (*time post-injury)*	Baseline (*0–6 weeks)*	1 (*12 weeks)*	2 (*26 weeks)*
Demographic data	X		
Type of injury (TBI/stroke)	X		
EuroQoL-5D-3L		X	X
mRS	X	X	X
FIM™	X	X	X
HADS	X	X	X
Participant satisfaction		X	X
Modified Caregiver Strain Index (administered to participant’s caregiver)		X	X

### Randomisation of sites

Since the rural sites are smaller in size and were expected to recruit fewer participants, a restricted randomisation strategy was considered appropriate. Moreover, due to differences in the availability of advanced care in the four rural sites, patients are often transferred from these sites to one of the urban sites. Therefore, for the purpose of randomisation, each rural site was paired with the urban site to which it usually transfers patients for acute care as needed. The four pairs formed by this process were treated as clusters for the purposes of randomisation. These clusters were designated as A, B, C or D by the trial data and operations manager. The trial statistician who was blinded to this designation, then generated the sequence in which the clusters would cross over to the intervention condition, using simple randomisation.

### Recruitment and allocation of participants

The trial used a continuous recruitment strategy [23, 24]. All eligible participants who presented to a participating site in the trial period were invited to participate. Participants who accepted the invitation were allocated to the trial intervention phase (control or intervention) that the site was undergoing at the time of their recruitment.

### Patient population

The patient population consisted of Aboriginal Australians, 18 years or older who presented at one of eight hospital sites in Western Australia during the trial period after having experienced either an acute stroke or traumatic brain injury and were within 6 weeks post event. Participants had to have a neurological deficit present as reflected on the NIHSS [25] (stroke patients). Patients with TBI could not have a Glasgow Coma Scale (GCS) [26] of < 8. All had to be deemed to be able to benefit from rehabilitation by their medical and allied health team. Further detailed inclusion and exclusion criteria are provided in the published study protocol [16].

### The intervention

The trial implemented a complex intervention consisting of cultural security training for hospital staff and the employment of Aboriginal Brain Injury Coordinators (ABIC) to see the participants in hospital and up until 26 weeks post-injury onset and provide education, support, liaison and advocacy services to the participants and their families. The cultural security training involved workshops training 20 health professionals at each site (nursing, medical and allied health staff). The workshops were offered every 6 months during the intervention period for the site and consisted of a 3-h face to face component and 3 h of online modules. The Aboriginal Brain Injury Coordinator component required the Coordinator to be in contact with the participant a minimum of six times following their injury on a monthly basis during the intervention period.

### Sample size

Our sample size estimation procedure involved three steps. In the first step, we conducted a naïve sample size estimation which ignored the clustering effects of data collected through the stepped wedge design. In the second step, we calculated the design effect of the stepped wedge, using the method presented by Woertman et al. [27]. We then calculated the total sample size required by multiplying the naïve sample size calculated in the first step by the design effect and the total number of time periods in the planned design.

Our estimation was based on our primary outcome measure of Euro QOL–5D [17] VAS. We did not have any studies or preliminary data on the use of this measure in Aboriginal Australian populations. Therefore, our estimate of the effect of the intervention was based on the mean difference on the Euro QOL–5D [17] VAS between stroke and non-stroke populations in the published literature. Based on the literature [28, 29], the mean difference between stroke and non-stroke populations on the Euro QOL–5D [17] VAS was approximately 25 points with a standard deviation of 25. Guided by this information, we assumed that the intervention would result in an improvement of 15 points on the Euro QOL–5D [17] VAS (with a standard deviation 25), which equates to a standardised effect size of d = 0.6 for an independent sample t-test.

Using GPower 3.1 [30], we estimated the naïve sample size for an independent samples t-test and calculated that we would require a total of 90 participants to detect our estimated difference of d = 0.6 with 80% power at the 5% significance level.

The design effect proposed by Woertman et al. [27] is based on the number of clusters, number of steps, number of measurements at the end of each step and number of baseline measurements. Our proposed design had four clusters which were randomised to commence intervention in four steps, one baseline measurement and one measurement at the end of each step. We assumed a conservative intraclass correlation of 0.08. Based on these inputs, we calculated a design effect of 0.56. Multiplying the naïve sample size (n = 90) by the design effect (DEsw = 0.56) and the number of time periods in the trial (n = 24), and rounding-up our results to ensure that the number of patients per cluster per time period was an integer, we obtained a total sample size of 312 or 13 per cluster per time period.

We note that this approach may have over-estimated the required sample size since our design:Incorporates an extra follow-up period which is not accounted for in the estimation.Calls for two measurements for each individual (at each step): one at 12 weeks and the second at 26 weeksIncludes a round-up error by ensuring an integer value of participants in each cluster in each time period.

However, since we had little or no prior information in our estimates of effect size and intraclass correlation coefficient, this conservative approach in our estimation of total sample size was appropriate. Moreover, our estimate allowed for a 4% drop-out rate. Due to pragmatic considerations including the sparse distribution of the trial population in remote geographical regions, the estimated sample size was believed to be the maximum that could be achieved within the trial timeframe. Therefore, no additional allowance for drop-out was included in our sample size estimation.

### Blinding

All assessors were independent of the researchers involved in the intervention or the trial. Since the implementation of the intervention involved providing the treating clinicians with cultural security training, blinding of the treating clinicians was not possible. Similarly, since the intervention required the participant and/or the participant’s next of kin to interact with the ABIC, it was expected that the participants would be aware if they were receiving intervention. Therefore, the participants are not considered to have been blinded.

### Assessments

Participants were assessed at three timepoints on the outcome measures outlined below—within 6 weeks of injury and at 12 and 26 weeks post-injury (see Table 1).

Demographic data, injury type and severity, functional independence measures and hospital anxiety and depression were recorded at the baseline assessment.

### Primary outcome measure

The primary endpoint is the Euro QOL–5D-3L [17] VAS at 26 weeks post-injury.

### Secondary participant-level outcome measures

#### Participant outcome measures

The secondary participant-level outcome measures are:The modified Rankin Scale (mRS) [18]The Functional Independence Measure (FIM) [19]The Hospital Anxiety and Depression Scale(HADS) [21]Participant satisfaction

In addition, the Euro QOL–5D-3L [17] VAS at 12 weeks post-injury is considered a secondary outcome which will be reported in descriptive statistics but is not the subject of any hypotheses.

#### Caregiver outcome measures

The Modified Caregiver Strain Index [20] was administered at 12 weeks and 26 weeks post-assessment.

#### Other participant-level data

Demographic data collected at time of recruitment includes:AgeGenderRecruitment siteLiving arrangements prior to injuryStroke/brain injury risk factors, e.g. hypertension, diabetes, alcohol consumption, adverse events (AEs) and serious adverse events (SAEs) that occurred while a participant was enrolled in the trial were recorded when notified.

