### Safety assessments

Adverse events (AEs) are classified as possibly, probably or definitely attributable to the intervention. Serious adverse events (SAEs) are classified as not related, unlikely, possibly, probably or definitely attributable to the intervention as they occur (between consent and 26 weeks post brain injury). AEs and SAEs will be reported by condition (control/intervention) in the main paper. The structure of this table is presented in Table 6 of Appendix.

AEs and SAEs possibly, probably or definitely attributable to the intervention are expected to be rare. Therefore, no formal hypotheses are associated with these. As rare events, AEs and SAEs are expected to have a Poisson or a negative binomial distribution. If the data suggests that there is a between-condition difference of more than 3 standard deviations in AEs or SAEs, the distribution will be modelled, and an appropriate generalised linear model will be developed to assess between-condition differences.

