**System-level outcomes**			
Minimum Processes of Care Achieved (Yes)			
Occasions of Service

**Table 6 Tab6:** Adverse events and serious adverse events

	**Control**	**Intervention**	**All**
	*n* (%)	*n* (%)	*n* (%)
No. of adverse events (AEs)			
Neurological complications			
0			
1			
2			
> 2			
No. of serious adverse events (SAEs)			
0			
1			
2			
> 2

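### AEs and SAEs were recorded when notified, but intervention participants have extra coordinator contacts, so the by-condition safety comparison may reflect contact frequency as well as harm

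*SAP article*

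**What the plan says.** **Capture.** Under Other participant-level data, adverse events and "serious adverse events (SAEs) that occurred while a participant was enrolled in the trial were recorded when notified". The article does not say who notifies. Tables 1 and 2, the schedules of participant-level and system-level outcome measures, list no enquiry about events.

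**Contacts in both conditions.** Under Assessments, "Participants were assessed at three timepoints on the outcome measures outlined below": baseline, 12 weeks and 26 weeks. Study design adds that the two follow-up assessments took place mostly off-site, after discharge.

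**Contacts in the intervention condition only.** Coordinators are employed "to see the participants in hospital and up until 26 weeks post-injury onset", and this component "required the Coordinator to be in contact with the participant a minimum of six times following their injury on a monthly basis".

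**Use of the counts.** Under Safety assessments, "AEs and SAEs will be reported by condition (control/intervention) in the main paper", in the layout of Appendix Table 6. The safety window for SAEs runs from consent to 26 weeks after injury. There is no formal safety hypothesis, but a between-condition difference of more than 3 standard deviations in AEs or SAEs leads to a generalised linear model.

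**The concern.** A comparison of event counts is fair only if the same event has about the same chance of being recorded in each condition. Here recording depends on notification, and the intervention itself adds occasions on which an event can come to light. Those occasions largely fall inside the safety window. The same fall or minor complication at home could be mentioned to a coordinator in one phase and go unreported in the other.

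The likely direction is over-counting under intervention relative to control. That could produce an apparent harm of the coordinator service, trip the modelling trigger without a true excess, or hide a true reduction in events. A larger sample would not remove the problem, because the extra contacts are tied to condition. With 108 participants, a few differently notified events could change the picture in Table 6. Nothing in the article equalises ascertainment, restricts the comparison or states the limitation.

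**Working it through.** The article gives no event rate, notification probability or safety power, so there is no figure of its own to reproduce. What follows is an illustration.

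**Inputs from the article**
- Follow-up contacts in both conditions: weeks 12 and 26 (Table 1).
- Extra contacts under intervention: six, monthly, up to week 26 (The intervention).

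**Assumptions**
- Event times are uniform over weeks 3 to 26, a span of 23 weeks, with the same true rate in both conditions.
- Monthly means every 26/6 = 4.33 weeks: weeks 4.33, 8.67, 13, 17.33, 21.67 and 26. The sixth coincides with the 26-week assessment and is not counted twice, so five distinct contacts are added.
- Each contact after the event brings it to notice with probability p, independently.

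**Formula.** An event followed by k contacts is captured with probability 1 − (1 − p)^k, averaged over event times.

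**Contacts after an event**
- Control: k = 2 for events in weeks 3 to 12 (9/23 = 0.391) and k = 1 in weeks 12 to 26 (14/23 = 0.609). Mean 2 × 0.391 + 0.609 = 1.39.
- Intervention: k = 7, 6, 5, 4, 3, 2, 1 over successive intervals of 1.33, 4.33, 3.33, 1, 4.33, 4.33 and 4.33 weeks. Mean 82/23 = 3.57.

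**Example, p = 0.3.** Control: 0.391 × 0.51 + 0.609 × 0.30 = 0.382. Intervention: 1 − [1.33 × 0.7^7 + 4.33 × (0.7^6 + 0.7^3 + 0.7^2 + 0.7) + 3.33 × 0.7^5 + 1 × 0.7^4]/23 = 0.649.

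| p | Captured, control | Captured, intervention | Apparent ratio |
|---|---|---|---|
| 0.3 | 0.382 | 0.649 | 1.70 |
| 0.5 | 0.598 | 0.824 | 1.38 |
| 0.7 | 0.782 | 0.921 | 1.18 |
| 0.9 | 0.935 | 0.979 | 1.05 |

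Deaths and other events that a 12- or 26-week assessment readily reveals belong near the bottom row. Minor events belong nearer the top.

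**Effect on a 3-unit trigger.** The article does not define the standard deviation in its trigger. I read it as (I − C)/√(I + C) ≥ 3 for Poisson counts I (intervention) and C (control), and assume 54 participants per condition, since the split by condition is not shown. Expected counts are 54 × true rate × capture. With equal capture (0.5 and 0.5), the chance of crossing with no true excess is about 0.1%. With capture 0.5 against 0.75 (ratio 1.5, within the range above):

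| True events per participant | Expected count, control | Expected count, intervention | Chance of crossing |
|---|---|---|---|
| 0.3 | 8.1 | 12.15 | 1.3% |
| 0.5 | 13.5 | 20.25 | 3.0% |
| 1.0 | 27 | 40.5 | 8.4% |

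The trigger would still be crossed rarely in these scenarios, but more often than under equal ascertainment.

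**The case against.** How events are elicited is normally protocol content, and the article refers to a published protocol that is not shown. The clause on notification is half a sentence attached to a list of demographic items. A reader might infer that events were captured only by spontaneous report, or that coordinators were a reporting route. The article says neither: it does not name who notifies, and it gives coordinators education, support, liaison and advocacy. Assessors may have asked about events at 12 and 26 weeks, and hospital staff or family could notify in either phase. The absence of events from Tables 1 and 2 shows little, since those tables schedule outcome measures.

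These points limit the size and certainty of the concern but do not remove it. Even with enquiry at 12 and 26 weeks, the extra contacts belong to one condition.

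Three stronger readings are not supported.
- **A doubling or tripling of apparent events.** Counting the sixth contact and the 26-week assessment separately raises the ratio at p = 0.3 to 1.97. Comparing 2 with 8 contacts regardless of when the event happens gives 1.33 to 3.45 for p from 0.5 down to 0.05, but this credits contacts made before the event. Six contacts is also a requirement: the section on adherence expects to report how many participants reached it.
- **Silence coded as no event.** Table 6 is an empty shell and does not say how participants without follow-up are counted.
- **Existing extractions as a ready remedy.** Data management describes outpatient and inpatient allied health use and processes of care. It does not describe readmissions or SAEs.

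**Conclusion.** The concern holds in a limited form. The stated capture rule, the condition-specific contacts and the planned comparison together make notification opportunity likely to be higher under intervention. The by-condition table and the modelling trigger may therefore mix contact frequency with harm, mainly for less serious events.

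The size is unknown. The illustrative ratios of about 1.05 to 1.7 rest on an assumed notification probability, uniform event times and full delivery of the monthly contacts. Incomplete delivery, or notification through hospital staff or family, would bring them closer to 1. The document does not show that the safety comparison is in fact biased by any given amount.

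The consequence is confined to the interpretation of safety. The primary outcome and the secondary hypotheses are untouched. This is an inexpensive improvement to the analysis plan, not a fault that undermines it.

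**What to change.** In Safety assessments and Table 6:
1. Keep the table of all AEs and SAEs by condition.
2. Flag the source of each event where it is recorded.
3. Base the between-condition comparison and the 3-standard-deviation trigger on events from routes common to both conditions: deaths (mRS 6, from the undichotomised score) and events found at the 12- and 26-week assessments. Add the resource-utilisation questionnaire or records only if they prove to hold such events.
4. List events known only through a coordinator in a separate row. An event found by both a coordinator and a common route stays in the comparison.
5. For the row of zero events, give the denominator actually followed to 12 and 26 weeks.
6. State that any difference in all events is to be read with unequal contact in mind.

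The cost is some wording and one further split of Table 6. Fewer events enter the comparison. Follow-up ended on 31 January 2022 and database lock was expected on 18 March, so sources may have to be assigned retrospectively. If an event already reported by a coordinator was not entered again at the assessment, the restricted comparison could under-count the intervention condition, and this should be checked when sources are assigned.
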